#### 4.1 Name and Description of Investigational Product

MGS0274 besylate is the active ingredient of TS-134 investigational product. MGS0274 is a prodrug, converted to the active metabolite MGS0008 upon enzymatic hydrolysis. MGS0008 is a selective agonist for mGlu2 and mGlu3 receptors. In all cases, dosed or measured mass of MGS0274 or MGS0008 are expressed as free base.

- Chemical Name: (1S,2S,3S,5R,6S)-2-Amino-3-fluoro-6-(((1S)-1-([[(1R,2S,5R)-5-methyl-2-(propan-2-yl)cyclohexyl]oxy}carbonyl)oxy]ethoxy}carbonyl)bicyclo[3.1.0]hexane-2-carboxylic acid monobenzenesulfonate
- Molecular Formula: C21H32FNO7 · C6H6O3S
- Molecular Weight: 587.65 (as besylate salt)

Additional details on investigational product including excipients can be found in the TS-134 Investigator's Brochure.

Confidential

[REDACTED]

## **5 STUDY OBJECTIVES**

### **5.1 Primary Objective**

- To evaluate the treatment effects of TS-134 on ketamine-induced BOLD signals in pre-specified regions of interest (ROIs) in resting fMRI

### **5.2 Secondary Objectives**

- To evaluate the treatment effects of TS-134 on ketamine-induced BOLD signals in whole brain in resting fMRI
- To evaluate the treatment effects of TS-134 on scores of the Brief Psychiatric Rating Scale (BPRS) and the Clinician Administered Dissociative States Scale (CADSS)
- To evaluate safety of multiple dose titrations of TS-134

## 6 STUDY DESIGN AND EVALUATION

### 6.1 Study Design

This study employs a randomized, single-blind, parallel-group design in healthy volunteers.

This study will enroll approximately 60 subjects. Following an up to 27-day outpatient Screening Period, eligible subjects will undergo an 8-day inpatient Treatment Period. Subjects will be randomized to one of three treatment groups in a ratio of 5:5:2 (25 subjects for a TS-134 20 mg group, 25 subjects for a TS-134 60 mg group and 10 subjects for a placebo group) (Figure 6-1). During the study, each subject will undergo a total of two ketamine sessions; a first session during a Screening Period and a second session on Day 6 of a Treatment Period. Each ketamine session will include one ketamine infusion with resting fMRI scanning from pre to post ketamine infusions. First and second ketamine sessions will be conducted at least 7 days apart. All randomized subjects will be dosed with TS-134 or placebo daily in a fed state, for 6 days during the study. TS-134 dose levels will be titrated according to the titration schedule shown in Table 6-1. Subjects' general health and safety status will be confirmed by a phone call one week following discharge from a Treatment Period.

[figure not shown]

Figure 6-1 Study Design

**Table 6-1 Treatment Titration Scheme**

| Treatment Group    | No. of Subjects | Treatment Period |       |       |       |       |       |       |       |
|--------------------|-----------------|------------------|-------|-------|-------|-------|-------|-------|-------|
|                    |                 | Day -1           | Day 1 | Day 2 | Day 3 | Day 4 | Day 5 | Day 6 | Day 7 |
| TS-134 20 mg group | 25              | -                | P     | P     | 10 mg | 10 mg | 20 mg | 20 mg | -     |
| TS-134 60 mg group | 25              |                  | 10 mg | 10 mg | 20 mg | 40 mg | 60 mg | 60 mg |       |
| Placebo group      | 10              |                  | P     | P     | P     | P     | P     | P     |       |

P = placebo

### **Premature Discontinuation:**

Subjects may discontinue study participation at any time in this trial. All randomized subjects who prematurely discontinue participation after receiving at least one dose of investigational product will be followed-up by telephone by study staff approximately 1 week after their last dose administration (Early Termination (ET) Phone Call Follow-Up). Subjects who discontinue from the study prior to completion of the ketamine BOLD assessment on Day 6 may be replaced at the sponsor's discretion. See Section 8.4 for further details pertaining to early discontinuation procedures.

## **6.2 Study Endpoints**

### **6.2.1 Primary Endpoint**

Changes in ketamine-induced BOLD fMRI signals in pre-specified ROIs (anterior cingulate cortex (ACC) and anterior insula) following administrations of TS-134

### **6.2.2 Secondary Endpoints**

- Changes in ketamine-induced BOLD fMRI signals in whole brain following administrations of TS-134
- Changes in BPRS scores following administrations of TS-134
- Changes in CADSS scores following administrations of TS-134
- Changes in safety parameters following administrations of TS-134

## 7 STUDY POPULATION

This study will be conducted in approximately 60 healthy male and female volunteers. These subjects are defined by the inclusion and exclusion criteria described in the following sections.

### 7.1 Inclusion Criteria

Subjects must meet all of the following inclusion criteria to be eligible for enrollment:

1. Healthy adult male and female subjects between 18 and 55 years of age inclusive (at the time of initial informed consent).
2. Body weight  $\geq 45$  and  $\leq 87$  kg at Screening Visits.
3. Body Mass Index (BMI)  $\geq 18$  and  $\leq 30$  kg/m^2 at Initial Screening Visit using the following formula:  
$$\text{weight (kg)} / [\text{height (m)}]^2.$$
4. Female subjects of child-bearing potential must agree to use one of the accepted barrier methods of contraception (listed below) during the trial (including the Screening Period), and at least 90 days after stopping the investigational product.
  - a. condom (male or female) with spermicide,
  - b. diaphragm or cervical cap with spermicide and condom (male),

Note: Oral contraception, vasectomy of the partner and IUD alone are not considered sufficient contraception. One of the aforementioned methods listed above must be used. Females who are not currently sexually active must also consent to use one of these accepted methods of contraception should they become sexually active while participating in the study.

Female subjects of non-childbearing potential must be either surgically sterile (i.e., documentation of hysterectomy or bilateral oophorectomy) or post-menopausal (absence of spontaneous menses for 12 consecutive months).

Male subjects should refrain from fathering a child or donating sperm during the study and for at least 90 days following the last dose of TS-134.

5. The subject is able and willing to provide written informed consent and authorization for protected health information disclosure in accordance with Good Clinical Practice (GCP).

### 7.2 Exclusion Criteria

Subjects are to be excluded from study participation if they meet any of the following exclusion criteria:

1. Female subjects who are pregnant, intend to become pregnant (within 90 days of the last dose), or are breastfeeding. Positive serum/urine pregnancy test results at Screening Visits or Day -1 (Admission) will disqualify a subject from study participation.

2. Clinically significant abnormal values for hematology, biochemistry or urinalysis at the Initial Screening Visit. It is expected that the values will generally be within the normal range for the laboratory, however minor variances, where they are considered not to be clinically significant per the investigator, are acceptable.
3. Clinically significant abnormal physical examination, vital signs OR 12-lead electrocardiogram (ECG) at Screening Visits (except for Final Screening Visit: Discharge) or Day -1 (Admission).
4. Significant history or presence of hepatic, renal, cardiovascular, pulmonary, gastrointestinal, hematological, locomotor, immunologic, ophthalmologic, metabolic or oncological disease.
5. History or presence of psychiatric or neurologic disease or condition (including but not limited to any psychosis, schizophrenia, bipolar disorder, epilepsy, closed head trauma with unconsciousness, partial onset seizures etc.), confirmed through a Structured Clinical Interview for DSM-5 disorders – Clinical Trials Version (SCID-5-CT).
6. History of first-degree relative with schizophrenia or mood disorder with psychosis.
7. Recent history (within previous 6 months) of alcohol or drug abuse (as judged by the investigator) or has consumed > 2 alcohol drinks/day during the last 3 months prior to screening (1 glass is approximately equivalent to: beer [284 mL/ 10 ounces], wine [125 mL/ 4 ounces], or distilled spirits [25 mL/ 1 ounce]). Subjects that consume 3 glasses of alcoholic beverages per day, but less than 14 glasses per week, may be enrolled at the discretion of the investigator. Positive urine/saliva screen for alcohol or controlled substances at Screening Visits or Day -1 (Admission) will disqualify a subject from study participation.
8. History of recreational ketamine use, recreational PCP use, or an adverse reaction to ketamine. Subjects who have participated in prior research ketamine studies will be eligible providing they have participated in no more than 5 previous research ketamine infusions. Subjects can have infusions not more frequently than biweekly, and not more than 1/month on average, therefore subjects will need to wait 1 month if they had a single infusion and 6 weeks if they have had 2 closely spaced infusions prior to screening into the study.
9. Any subject who is unable to refrain from smoking throughout the study or with positive urine cotinine screen (> 400 ng/mL) at the Initial Screening Visit.
10. Any subject with a history and/or current evidence of serologic positive results for hepatitis B surface antigen, hepatitis C antibodies, or HIV antibodies 1 and 2 at the Initial Screening Visit.
11. History of violence, including any history of using a gun, knife, or other weapon with intent to harm someone, as well as a more than one physical fight without a weapon after the age of 18 years old (not including fights that happen during sports competition).

12. Presence or positive history of significant medical illness, including high blood pressure (SBP > 140 mmHg, DBP > 90 mmHg), low blood pressure (SBP < 100 mmHg, DBP < 60 mmHg), orthostatic hypotension (change in mean arterial pressure [ $1/3$  systolic +  $2/3$  diastolic] of > 20%) at Screening Visits (except for Final Screening Visit: Discharge) or Day -1 (Admission).
13. Any subjects who show subthreshold ketamine BOLD response (defined as % BOLD signal change of 0.5% at peak ketamine response) in ACC at Final Screening Visit.
14. Metal implants, pacemaker, other metal (e.g. shrapnel or surgical prostheses) or paramagnetic objects contained within the body which may present a risk to the subject or interfere with the MR scan, as determined in consultation with a neuroradiologist and according to the guidelines set forth in the following reference book commonly used by neuroradiologists: *Guide to MR procedures and metallic objects, F. G. Shellock, Lippincott Williams and Wilkins Philadelphia 2001*.
15. Claustrophobia.
16. Donation of one or more units of blood, plasma, or acute loss of an equivalent amount of blood within 60 days prior to Initial Screening Visit. (One unit= 450mL)
17. Use of any prescription or over-the-counter medication (including medicinal patch), herbal medication, vitamins, or mineral supplements within 14 days prior to administration of the investigational product. Medicinal patch, if used during the Screening Period, must be removed prior to the MRI scan.  
Acetaminophen up to 3 g per day will be allowed, as well as non-steroidal topical preparations, eye drops for dry-eye that does not contain any active ingredient, oral contraceptives and hormonal replacement.
18. Any subject with previous exposure to the investigational product or who is known to be allergic to the investigational product or any components of the investigational product.
19. Any subject who has received treatment with a drug that has not received regulatory approval for an indication during the 30 days prior to screening.
20. Subject with any history of suicidal behavior or is currently at risk of suicide in the opinion of the investigator, or who has answered 'YES' to questions 1 or 2 on the Columbia - Suicide Severity Rating Scale (C-SSRS) at Final Screening Visit or Day -1 (Admission).
21. Participated in strenuous exercise within 48 hours prior to the initial dosing of the investigational product and/or are unwilling to avoid strenuous exercise at any time throughout the study.
22. Investigative site personnel or their immediate families (spouse, parent, child or sibling whether biological or legally adopted).
23. Taisho employee or their immediate families (spouse, parent, child or sibling whether biological or legally adopted).

24. Any subject not able to meet the study requirements.

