#### 8.1.2 Handling and Dispensing of Investigational Product

Investigational drug product components (powders) and all drug product solutions prepared at the study site should be stored at 5°C ± 3°C. Following preparation of each dose-level-specific dosing solution, a retention sample will be prepared and stored for possible shipment to the sponsor. Detailed instructions for preparing and handling TS-134 and placebo oral solutions and any retention samples will be provided in a separate pharmacy manual.

TS-134 and placebo will be administered orally as a solution, along with 240 mL of water. If subjects are not able to drink 240 mL of water completely, subjects' actual water intake will be recorded in the subjects' study records. The investigational product solution will be administered daily (every 24 hours) beginning on the morning of Day 1 and continue through Day 6, within 15 minutes after completing a standard breakfast. Water will be permitted *ad libitum* except for 1 hour before and 1 hour after each dose. A taste-masking product (e.g. Listerine PocketPaks breath strips) will be used immediately before and after daily dosing.

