## **8.2 Concomitant Drug Therapy**

Subjects are prohibited from taking any prescription, over-the-counter (including medicinal patch) or herbal medication, vitamins or mineral supplements within 14 days prior to administration of their investigational product, and for the duration of the study. A medicinal patch, if used during the Screening Period, must be removed prior to the MRI scan. The exception of racemic ketamine and saline used for the study procedure, acetaminophen in the amount of up to 3g per day, non-steroidal topical preparations, eye drops for dry eye that does

not contain any active ingredient, as well as oral contraceptives or hormonal replacement will be allowed.

If the subject requires any concomitant therapy for an adverse event, it must be reported in the subject's study records. Any changes to the concomitant therapy during the study must be clearly recorded and the reason for the change should be documented.

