### **8.3 Duration of Subject Participation**

This study is comprised of the following:

- Screening Period of up to 27 days (Day -28 to Day -2)
- Treatment Period of 8 days (Day -1 to Day 7)
- Phone Call Follow-up on Day 14

Subjects will make 3 visits (2 outpatient visits during a Screening Period and 1 inpatient visit for a Treatment Period) to the study site. The overall time to participate in this study is approximately 2 to 6 weeks.

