## **10.5 Pharmacodynamics (PD) Analysis**

### **10.5.1 Primary Endpoint**

To evaluate the treatment effect of TS-134 on ketamine-induced BOLD signals in pre-specified ROIs (ACC and anterior insula) in resting fMRI, analysis of covariance (ANCOVA) with change from baseline at Day 6 BOLD as the outcome predicted by baseline (Final Screening Visit) BOLD and treatment in 3-treatment groups (TS-134 20 mg group, TS-134 60 mg group and placebo group) will be performed, and the mean and 95% confidence interval (CI) will be estimated. Separate ANCOVAs will be fit to each ROI. Tests of treatment effect will be made within each treatment group, between each active treatment group (TS-134 20 mg group and TS-134 60 mg group) versus placebo group, and also between the two active treatment groups from the ANCOVA. A statistically significant negative change of BOLD found in the active treatment groups compared to placebo group would be consistent with the hypothesis. Cohen's d effect sizes will be reported using the standard deviation of baseline BOLD.

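### The 14-day medication-free window is counted back from the first TS-134 dose, so it does not guarantee 14 medication-free days before the ketamine session that supplies the baseline

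*Protocol*

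**What the plan says.** Exclusion 17 (Protocol 7.2) excludes subjects who use prescription or over-the-counter drugs, herbal products, vitamins or "mineral supplements within 14 days prior to administration of the investigational product". It then lists permitted products and adds: "Medicinal patch, if used during the Screening Period, must be removed prior to the MRI scan". Section 8.2 repeats the ban as running "within 14 days prior to administration of their investigational product, and for the duration of the study", with the same patch rule and a similar permitted list.

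Section 8.1.2 has dosing "beginning on the morning of Day 1 and continue through Day 6". Section 6.1 places the two ketamine sessions as "a first session during a Screening Period and a second session on Day 6 of a Treatment Period". Section 8.3 sets screening at up to 27 days, Day -28 to Day -2.

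The first session carries much of the analysis. In Section 10.5.1 the change in BOLD at Day 6 is "predicted by baseline (Final Screening Visit) BOLD and treatment", and Cohen's d is scaled by the SD of baseline BOLD. Section 10.5.2 treats BPRS and CADSS similarly. Exclusion 13 is judged on the ACC response at the same visit.

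**The concern.** The two ketamine scans should differ by study treatment and as little else as possible. The protocol pursues this elsewhere: Section 9.3.5.1 holds the second scan within 2 hours of the first scan's clock time, and alcohol and drug screens are repeated at the Final Screening Visit. The medication rule alone is tied to a later event, the first dose.

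A subject could therefore be scanned at baseline while taking, or shortly after stopping, a drug that is absent on Day 6. The change score would then include the effect of stopping that drug. Four results could be affected: the change from baseline within each arm, the precision of the comparison between arms, the baseline SD that scales Cohen's d, and the decision on whether a subject's ACC response is subthreshold.

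**Working it through.** **Calendar.** Day -28 to Day -2 is 27 days, as Section 8.3 states. Its 8-day Treatment Period from Day -1 to Day 7 works only if there is no Day 0 (with a Day 0 it would be 9 days). Both stated figures are therefore reproduced with no Day 0.

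**Permitted first sessions.** Section 6.1 requires at least 7 days between sessions. Day -2 to Day 6 is 1 + 1 + 5 = 7 days, so all 27 screening days qualify by this rule. If the initial and final screening visits are on separate days, the earliest session is about Day -27, which does not change the conclusion.

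**Start of the window.** Fourteen days before Day 1 is Day -14.

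**Guaranteed medication-free days before each scan.** For a first session on Day s (s negative), this is max(0, s + 14).

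| Scan | Guaranteed medication-free days |
|---|---|
| First session, Day -28 to Day -15 (14 of 27 days) | 0; the session precedes the window |
| First session, Day -14 | 0 |
| First session, Day -7 | 7 |
| First session, Day -2 | 12 |
| Second session, Day 6 | 14 + 5 = 19 |

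No permitted date guarantees 14 days before the baseline scan. The 14 of 27 counts calendar days; it does not forecast how many sessions will fall there.

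**If the study-duration clause in Section 8.2 covers screening.** The ban would then start at consent or on Day -14, whichever is earlier. No minimum gap between the initial and final screening visits is stated. Consent on Day -20 with a session on Day -18 would guarantee 2 days. Fourteen days are not guaranteed on this reading either.

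**What a medicated baseline does to the estimates.** Suppose a fraction p of subjects in every arm has a baseline shifted by d, with Day 6 unaffected.

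- Within an arm, change is Day 6 minus baseline, so the mean change moves by -p × d. All arms' baseline means move together, so covariate adjustment does not remove it.
- Between arms, the equal shifts cancel. Randomization is on Day 1 (Section 9.2.2.2), after the baseline scan, so equal fractions are what to expect.
- By chance, one affected subject may fall in an arm of n. With slope b of Day 6 on baseline, the adjusted arm mean moves by about b × d / n. Assume d of 0.5 to 1 SD and b of 0.3 to 0.7; neither is in the protocol. The placebo arm (n = 10) then moves by 0.3 × 0.5 / 10 = 0.015 SD to 0.7 × 1 / 10 = 0.07 SD. For comparison, the standard error of a 25-versus-10 contrast is √(1/25 + 1/10) = √0.14 = 0.37 residual SD.

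**The case against.** A reader might infer that the gap biases TS-134 against placebo: a drug that heightens the ketamine response at baseline would mimic attenuation, and one that dampens it would hide attenuation. The documents do not support this. Baseline medication is fixed before randomization and is independent of arm, and Section 10.5.1 ties the hypothesis to the comparison with placebo. That comparison is exposed only to noise and chance imbalance.

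A reader might also infer that Section 8.2 cannot cover screening, because its 14-day clause and patch sentence would then be pointless. That is too strong. If screening lasts less than 14 days, the clause reaches back before consent. Exempt products such as hormonal replacement may come as patches, so the patch sentence does not prove that non-exempt drugs are foreseen. It suggests that the ban does not cover all of screening, and the wording remains unclear. Resolving it in the strict direction would still not guarantee 14 days before baseline.

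Affected subjects should be few. Exclusions 4, 5 and 12 remove significant medical, psychiatric and neurological illness. The title of one cited study refers to antipsychotic and glutamatergic agents attenuating the ketamine response, but people with psychosis are already excluded. Alcohol and ten listed substances are screened at the first ketamine visit, and prior medication is reviewed there. These safeguards are partial: for a session before Day -14, the anchored rule does not act on other medication found at that review.

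A wrong exclusion under item 13 loses a subject before randomization and does not bias the randomized comparison.

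**Conclusion.** The point holds as a cheap improvement. The medication-free window is anchored to the first dose and leaves the baseline session with 0 to 12 guaranteed days, against 19 before Day 6. This follows from the protocol's calendar alone.

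The between-group contrasts stay unbiased in expectation. They may lose some precision, and chance imbalance matters most in the 10-subject placebo arm; on the stated assumptions, one affected subject there is well inside sampling error. The planned within-group tests have no randomization to protect them and would carry the full average shift. The baseline SD behind Cohen's d may also be altered, and a subject may be misclassified under exclusion 13. How far any of this goes cannot be determined, because the protocol gives neither a medication effect nor the number of subjects likely to be affected.

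**What to change.** Reconcile exclusion 17, Section 8.2 and Section 8.3 so that the protocol's existing 14-day window and permitted list apply before the first ketamine session (Final Screening Visit) as well as before dosing, and continue for the rest of the study. State the rule once with a single end point, and say plainly whether the study-duration wording includes screening. Keep the requirement to remove any patch before the MRI scan. Apply the rule at the prior-medication review already scheduled for the Final Screening Visit.

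The cost is a wording amendment. Some volunteers would wait up to 14 days for the first session, or be screened out. A volunteer who stops a non-permitted product on Day -28 could be scanned from Day -14, which leaves 13 screening days. For sessions before Day -14 the window would open before Day -28, so the review must ask about medication taken before screening began. For a Day -28 session it would start 28 + 14 = 42 days before Day 1.
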